#### Randomization

Participants meeting all eligibility requirements are randomized to one of the three study arms in a 1:1:1 ratio in real time via an Internet data entry system that meets FDA requirements for electronic records and signatures (21 CFR part 11-compliant). A backup hard copy randomization scheme devised by the study statistician is used in case of Internet system failure. The study statistician has no contact with participants or the study staff who care for the participants. Data entry staff onsite record the study arm assignment for the enrolled participant. The participant then surrenders their current stock of TS and receives a supply of the study drug, if appropriate.

#### Blinding

Treatment arms are not masked as each has a different regimen (TS is once daily while CQ is once weekly), and because of the concern that a complicated placebo regimen may interfere with adherence to ART. This approach facilitates assessment of the effect of each prophylaxis regimen on treatment adherence. Laboratory technicians and the independent committee reviewing potential WHO stage 3 and 4 events are blinded to participant treatment assignment, whereas clinical staff are not.

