• Progressive multifocal leukoencephalopathy (PML)
• Candida of trachea, bronchi or lungs
• Chronic cryptosporidiosis
• Chronic isosporiasis
• Disseminated mycosis (histoplasmosis, coccidiomycosis)
• Recurrent septicemia (including nontyphoidal *Salmonella*)
• Lymphoma (cerebral or B-cell non-Hodgkin)
• Invasive cervical carcinoma
• Atypical disseminated leishmaniasis
• Symptomatic HIV-associated nephropathy or symptomatic HIV-associated cardiomyopathy

Antiretroviral therapy: continued in all participants as per Malawi Ministry of Health guidelines.

Secondary endpoints: undetectable (less than 400 copies/mL) HIV viral load and CD4 cell count assessed every 24 weeks, incidence of WHO HIV stage 2-, 3- or 4-defining illnesses or death, the occurrence of any suspected and laboratory-confirmed infection with bacteria or malaria, the occurrence of grade 3 or above adverse events (AEs) and rate of discontinuation of TS or CQ prophylaxis.

Sample size: 1400–1500 participants (approximately 1000–1100 from Blantyre and 400–500 from Zomba).

Study sites: Blantyre and Zomba, Malawi.

Study sponsor: US National Institutes of Health, National Institute of Allergy and Infectious Diseases, Division of Acquired Immunodeficiency Syndrome.

Study duration (recruitment and follow-up): 5.5 years.

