### Primary endpoint

The occurrence of a severe event (WHO stage 3 or 4 event or death).

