#### Clinical: incidence of WHO HIV stage 2-, 3- or 4-defining illnesses or death

In addition to the severe event outcomes listed in the primary endpoint section, the capacity of TS or CQ prophylaxis to prevent WHO stage 2 illnesses will be evaluated to permit assessment of a broader range of disease and illness prevention.

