#### The occurrence of all suspected and also laboratory-confirmed infection with bacteria or malaria

TS prophylaxis is expected to prevent both malaria and bacterial infections. Other studies document TS prophylactic efficacy in areas of underlying high rates of bacterial and malarial resistance [3, 4, 19], and the current study will evaluate the effect of TS in this population. Due to the return of CQ-sensitive *Plasmodium falciparum* to Malawi, CQ is expected to be highly efficacious at preventing malaria, but not opportunistic infections.

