Relationship to study products	Definitely related	The adverse event and administration of the study agent are related in time, and a direct association can be demonstrated	
	Probably related	The adverse event and administration of the study agent are reasonably associated in time, and the adverse event is more likely explained by the study agent than other causes	
	Possibly related	The adverse event and administration of the study agent are reasonably related in time, and the adverse event can be explained equally well by causes other than the study agent	
	Probably not related	A potential relationship between the study agent and the adverse event could exist (i.e. the possibility cannot be excluded), but the adverse event is most likely explained by causes other than the study agent	
	Not related	The adverse event is clearly explained by another cause not related to the study agent	
	Pending	Pending may be used as a temporary relationship assessment only for death and only if data necessary to determine relationship to the study agent are being collected. The site is required to submit a final assessment within three business days after reporting the death. If no final assessment is made within three business days after the date of submission, the event will be assessed as possibly related to the study agent. Any additional information received at a later time, including an autopsy report, should be submitted as a Follow-up Report	
Expectedness	Expected	Expected refers to the perspective of events previously observed, not on the basis of what might be anticipated from the pharmacological properties of the study agent	
		Study drug	Expected adverse events
		Trimethoprim-sulfamethoxazole	Rash, urticaria, loss of appetite, nausea, vomiting, agranulocytosis, aplastic anemia, disease of the hematopoietic system, fulminant hepatic necrosis, severe allergic reaction, Stevens-Johnson syndrome, and toxic epidermal necrolysis
		Chloroquine	Headache, malaise, dizziness, blurred vision, difficulty focusing, muscle weakness, electrocardiogram changes, gastrointestinal upset, mouth ulcers, diarrhea, vomiting, nonurticarial pruritis, leukopenia, methemoglobinemia, and retinopathy
	Unexpected	Unexpected refers to events whose nature or severity (intensity) is not consistent with those included in the package insert/summary.	

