### Discontinuation of study treatment assignment

If a participant is diagnosed with a WHO clinical stage 3 or 4 illness during the course of the study, or if their CD4 count is confirmed at below 200 cells/mm^3^, or they experience ART failure, they are given daily TS prophylaxis and followed according to the study protocol. If they had been assigned to CQ prophylaxis, the CQ will be stopped. They will not be withdrawn from the study for this reason.

If a participant becomes pregnant during the study, she will be given TS prophylaxis and remain in the study. If she was previously randomized to daily TS, she will continue taking daily TS. If she was previously randomized to take weekly CQ, she will discontinue weekly CQ. If she was previously randomized to no prophylaxis, she will begin taking daily TS. Pregnancy outcome information will be recorded on a pregnancy outcome case report form (CRF). When the participant is no longer pregnant, she may recommence the treatment to which she was originally assigned, if this is agreed to by the participant and the study team.

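### Illness is first diagnosed by staff who know the arm, the article does not say how potential stage 3/4 events reach the blinded committee, and no blinded review is described for stage 2 illness or suspected-only infection

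*Protocol article*

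**What the plan says.** The primary endpoint is "The occurrence of a severe event (WHO stage 3 or 4 event or death"). The Blinding section explains why the arms are not masked and then says who is: the laboratory technicians, and "the independent committee reviewing potential WHO stage 3 and 4 events are blinded to participant treatment assignment, whereas clinical staff are not". The Follow-up section has study clinicians record adverse events and evaluate illness. They use published diagnostic criteria where the setting allows.

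The section on discontinuing the study treatment assignment attaches a consequence to the diagnosis: "If a participant is diagnosed with a WHO clinical stage 3 or 4 illness during the course of the study", daily TS is given, and CQ is stopped in those assigned to it. A participant in the TS arm is already taking TS.

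Two secondary endpoints also matter here.
- **Clinical endpoint.** The overview lists "incidence of WHO HIV stage 2-, 3- or 4-defining illnesses or death". The endpoint's own section adds that "the capacity of TS or CQ prophylaxis to prevent WHO stage 2 illnesses will be evaluated". Table 1 includes recurrent oral ulceration in stage 2, and Table 6 lists among the expected effects of CQ "gastrointestinal upset, mouth ulcers, diarrhea, vomiting, nonurticarial pruritis".
- **Infection endpoint.** It is headed "The occurrence of all suspected and also laboratory-confirmed infection with bacteria or malaria". Any malaria sign or symptom leads to a smear, but a culture is taken only when bacteremia or meningitis is suspected.

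**The concern.** Blinded adjudication can reject a case that does not meet the definition. It cannot restore an event that never reaches it. The people who first decide whether an illness looks like stage 3 or 4 know the arm, and the label has a treatment consequence in two arms and none in the third. The stated main hypothesis is that TS is beneficial, so expectation is not neutral either. Because the primary question is noninferiority against a hazard ratio of 0.65, unequal capture can act on either error. Missing events off TS makes stopping look safer than it is, and missing events on TS costs power.

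The secondary endpoints are more exposed. Several stage 2 conditions rest on judgement, and the committee's described remit does not include them. They are combined with stage 3/4 illness and death in one outcome. In the CQ arm, a drug effect (mouth ulcers) could be counted as a failure to prevent HIV-related disease. Suspicion of infection is formed by staff who know whether the participant is taking an antibacterial or an antimalarial.

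**Working it through.** **1. Inputs from the protocol article.** Event rate 6.8 per 100 person-years (Abstract and Trial status). From Sample size and power calculations: 467 participants per arm, average follow-up 41.6 months, margin HR 0.65 (TS against none), one-sided 2.5%, about 196 first events in two arms, about 85% power.

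**2. Reproducing the plan's figures.**
- Mean events per participant: 0.068 × 41.6/12 = 0.2357 (stated 0.236).
- Probability of at least one event: 1 − exp(−0.2357) = 0.2100 (stated 0.210).
- First events in two arms: 2 × 467 × 0.2100 = 196.1 (stated 196).
- Power with SE = 2/√196 = 0.143: Φ(0.431/0.143 − 1.96) = Φ(1.06) = 85%, where 0.431 = −ln 0.65. This agrees with the plan, so no stated figure is in dispute.

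**3. Unequal capture (illustration only).** Let s_TS and s_none be the fractions of true events that are captured. The documents give neither; the values below are assumptions.
- Apparent HR = true HR × s_TS / s_none.
- Expected first events per arm: d = 467 × [1 − exp(−0.2357 × h × s)], where s is that arm's capture fraction, h is the true HR in the TS arm, and h = 1 in the no-prophylaxis arm.
- SE = √(1/d_TS + 1/d_none).
- Probability of declaring noninferiority = Φ([ln(apparent HR) − ln 0.65]/SE − 1.96).

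*True HR 0.65, events missed only in the no-prophylaxis arm (d_TS = 66.3):*

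| Missed | Apparent HR | d_none | SE | False-noninferiority rate |
|---|---|---|---|---|
| 0% | 0.65 | 98.1 | 0.159 | 2.5% |
| 5% | 0.68 | 93.7 | 0.161 | 5.1% |
| 10% | 0.72 | 89.3 | 0.162 | 9.5% |
| 20% | 0.81 | 80.3 | 0.166 | 26.9% |

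For the 10% row: ln(0.722/0.65) = 0.105; 0.105/0.162 − 1.96 = −1.31; Φ(−1.31) = 9.5%.

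*True HR 1, events missed only in the TS arm (d_none = 98.1):*

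| Missed | Apparent HR | d_TS | SE | Power |
|---|---|---|---|---|
| 0% | 1.00 | 98.1 | 0.143 | 85% |
| 5% | 0.95 | 93.7 | 0.145 | 75% |
| 10% | 0.90 | 89.3 | 0.146 | 60% |
| 20% | 0.80 | 80.3 | 0.151 | 28% |

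*Equal capture in both arms:* at 90% there are about 178 events and 82% power, and the error rate stays at 2.5%. The harm comes from the difference between arms, not from loss as such.

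**4. Which components have a blinded step.**

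| Component | Blinded step described | Exposure |
|---|---|---|
| Death | Not needed; vital status is sought for those no longer followed | Little |
| Stage 3 cytopenias | Blinded laboratory; blood count every 24 weeks in all arms | Little |
| Other stage 3/4 illness | Committee, once a case is put forward; selection rule not stated | Depends on that rule |
| Laboratory-confirmed malaria | Blinded reading; any sign or symptom prompts a smear | Small |
| Laboratory-confirmed bacterial infection | Blinded reading; taking the culture depends on suspicion | Partial |
| Suspected-only infection | None described | Full |
| Stage 2 illness | None described | Full |

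The calculation in step 3 spreads the missed events over all primary events. Because the first two rows are little exposed, a given percentage overall means a larger percentage among the judgement-based illnesses.

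**The case against.** The strongest reply is that the design is openly justified and better protected than it first appears. A reader might infer that the committee is the only blinded element; the same sentence blinds the laboratory technicians, which covers smears, cultures and blood counts. A reader might also infer that clinicians choose the committee's cases and that a missed event is never reviewed. The article says neither. It gives no selection rule, and such a rule commonly sits in the full protocol or a committee charter. Illnesses are recorded as adverse events in every arm, visits follow one schedule, and external monitors read hospital charts and clinicians' notes. All of this stands, and it limits the point on the primary endpoint to events that may go unreviewed.

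Two stronger numerical readings also fail. Over-referral off TS would not by itself cost power, since the extra cases would have to pass a blinded committee; the power loss shown above comes from under-capture on TS. Using the planning SE of 0.143 for the error rate gives about 35% at 20% under-capture, but fewer events are expected when the true HR is 0.65, and the figure is then about 27%.

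On the secondary endpoints, stage 3/4 illness or death is already analysed on its own as the primary endpoint, laboratory-confirmed infection is already named, and mouth ulcers touch one of eight stage 2 conditions, which must also be recurrent. These facts make the problem smaller. They do not supply a blinded review for stage 2 illness or suspected-only infection, or remove the overlap with a CQ effect.

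**Conclusion.** The point holds in a limited form. The text establishes that first diagnosis is unblinded, that a stage 3/4 diagnosis alters study prophylaxis in two arms only, that committee review is described for stage 3/4 events only, that stage 2 illness is combined with stage 3/4 illness and death, and that one stage 2 condition overlaps with an expected CQ effect. It does not establish that primary events are being lost, or in which arm.

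The size for the primary comparison is conditional on assumed capture: about 5, 10 or 27% false noninferiority for 5, 10 or 20% under-capture off TS alone, and about 60% power for 10% under-capture on TS alone. No size is given for stage 2 or suspected infection, because the documents state no event rate for either. The secondary endpoints carry the firmer part of the point, since it does not depend on how cases reach the committee.

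**What to change.** 1. Report stage 2 illness separately from committee-confirmed stage 3/4 illness or death, label it as an outcome assessed without blinding, and add a sensitivity analysis that leaves out recurrent oral ulceration.
2. Make laboratory-confirmed infection the leading infection outcome and suspected infection supportive. State that the decision to take a culture is still made by unblinded staff.
3. Confirm that one committee trigger list exists and is the same in all arms, or adopt one built from data already collected: all deaths, hospitalizations and other serious adverse events, positive cultures, and the Table 1 blood-count limits. This reduces dependence on unblinded staff but does not remove it, because seriousness, admission and culture decisions still involve them. If a charter already contains such a list, citing it is enough.

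The cost is some database queries, some extra committee cases and a few more analyses. No treatment rule or visit procedure changes.

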#### Enrollment

After randomization, baseline measurements of visual acuity using Snellen vision testing, and WHO performance score (Table 3) and bednet use (Table 4) are assessed and recorded. A dried blood spot specimen is obtained. The participant is then escorted to the study pharmacy. For those randomized to receive TS or CQ, a supply of the study drug will be given to each participant with instructions for how to take the medication. Participants will be asked to provide detailed directions to their home and of their contact cell phone number, if available, to facilitate active follow-up.

**Table 3 Tab3:** World Health Organization performance score

World Health Organization performance score	Definition
1	Asymptomatic, normal activity
2	Symptomatic, normal activity
3	Bedridden <50 % of the day during the last month
4	Bedridden ≥50 % of the day during the last month

**Table 4 Tab4:** Bednet use data collection

Uses bednet	☐ Yes	☐ No
If yes:		
Used most nights in last 4 weeks?	☐ Yes	☐ No
Used last night?	☐ Yes	☐ No

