### Toxicity management

For TS, related AEs are managed according to treatment guidelines based on the WHO grading scale for toxicity in adults and adolescents (http://www.who.int/hiv/pub/guidelines/ctxguidelines.pdf). Other AEs associated with the study drug will be managed by the study team.

For CQ, participants who experience a worsening in visual acuity (defined as a change in two levels or more using Snellen testing) or other visual complaints, muscle weakness, or hearing defects while taking CQ will discontinue CQ prophylaxis and will be referred to the ophthalmology or appropriate clinic for further evaluation and treatment. They will be placed on TS prophylaxis after CQ is discontinued.

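### Enrollment visual acuity, the only scheduled reading before chloroquine starts, is taken after the open-label arm is known, together with performance score and bednet use; reordering the visit would prevent this.

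*Protocol article*

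**What the plan says.** Under Enrollment, the protocol article states: "After randomization, baseline measurements of visual acuity using Snellen vision testing, and WHO performance score", and the same sentence adds bednet use. Only after these and a dried blood spot does the text continue: "The participant is then escorted to the study pharmacy".

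Under Randomization, the arm is assigned "in real time via an Internet data entry system", and "Data entry staff onsite record the study arm assignment for the enrolled participant". Under Blinding, "Treatment arms are not masked as each has a different regimen"; laboratory technicians and the event committee "are blinded to participant treatment assignment, whereas clinical staff are not".

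Table 2 ticks acuity, performance score and bednet use at Enrollment and at later visits, but not at Screening.

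Under Toxicity management, worsening acuity is "defined as a change in two levels or more using Snellen testing". When it occurs in a participant taking CQ, it leads to discontinuation of CQ. The rate of discontinuation of trimethoprim-sulfamethoxazole (TS) or CQ is a secondary endpoint.

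**The concern.** A baseline value is useful because it cannot depend on the arm. Here the three values are obtained when the participant and the assessor can already know it. All three are open to that knowledge. Snellen testing depends on effort and on how the examiner conducts the test, the performance score rests on reported symptoms and time in bed, and bednet use is self-reported.

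Acuity has the most at stake. An examiner who knows that a participant is about to start CQ might test more carefully, or record differently, than for someone in another arm. A better recorded baseline makes a later two-level worsening easier to reach, and a poorer one makes it harder. Either would shift the reference in one arm for a reason unrelated to the drug, and so could affect how often CQ is stopped.

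**Working it through.** No stated figure is in dispute, so the check sets the passages side by side.

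1. **Is the order really fixed?** Yes. The Enrollment section places the measurements after randomization in so many words. This is a stated sequence, not a detail left to a fuller document.

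2. **Is there an earlier value to fall back on?** No. Table 2 has no screening tick for any of the three. By contrast, the Screening section collects blood count, ALT, creatinine, CD4 count and viral load before allocation, so the plan already secures its laboratory baselines.

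3. **Can the arm be known at the time?** Yes. Assignment is in real time and recorded on site, and clinical staff are not blinded.

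4. **Could the drug itself affect the values?** Not under the Enrollment section's order, which puts the pharmacy after the measurements. The Randomization section mentions the handover of drug in its closing sentence, but it does not place that handover relative to the assessments. On the Enrollment order, any influence runs through testing or reporting alone.

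5. **Where are the values used?**
   - *Acuity.* The two-level change needs a reference. Toxicity management does not name one. The only reading that Table 2 schedules before dosing is the enrollment one; the next comes with the 24-week evaluations. A stop triggered this way counts towards the discontinuation endpoint.
   - *Performance score.* It is not among the endpoints, and the Analysis section describes no use of it.
   - *Bednet use.* It is likewise not an endpoint, and no adjusted analysis is described.
   - *Primary endpoint.* Death or a WHO stage 3 or 4 event uses none of the three, and potential stage 3 and 4 events are reviewed by a blinded committee. The primary comparison is TS continuation against discontinuation.

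6. **Would reordering alter the design figures?** No. The event expectation uses the event rate, follow-up and arm size only:
   - Mean events per participant: 6.8/100 × 41.6/12 = 0.236.
   - Probability of at least one event: 1 − exp(−0.236) = 0.210.
   - Participants with an event in two arms: 2 × 467 × 0.210 = 196.
   - Power against a hazard ratio of 0.65, one-sided 2.5%: Φ(|ln 0.65| × √196/2 − 1.96) = Φ(1.06) = 85.4%, matching the stated figure of about 85%.

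7. **How many could benefit?** Trial status reports 900 recruited by mid-February 2015 and an expansion of about 500–600. That is 500/1400 = 36% to 600/1500 = 40% of the total. It is an upper bound. A 36-month enrollment period counted from November 2012 would end about November 2015, and the article does not say how many of the added participants had already been enrolled.

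**The case against.** The strongest reply is that no analysis is shown to be harmed. The acuity rule is an individual safety trigger for people taking CQ, not a between-arm comparison of change in acuity. It sits beside other triggers (other visual complaints, muscle weakness, hearing defects), and TS is stopped under different rules, so the discontinuation comparison is asymmetric whatever the order at baseline. The reference for the Snellen change is inferred. Nothing shows that knowledge of the arm moves a reading by two levels, and the values do precede any study drug, which is what matters most for a safety reference. All later assessments remain open label.

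Most of this stands and limits the point. It does not remove it: a change rule needs a reference, only one pre-dosing reading is scheduled, and the reasons given for not masking (different regimens, ART adherence) do not require that reading to follow allocation.

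Two stronger readings might be inferred, and neither is supported.
- **That a bednet-adjusted malaria analysis would be biased.** The article names no covariate and describes no such model.
- **That participants without malaria protection would change their net use and so distort the baseline.** Table 4 asks about the preceding four weeks and the previous night. Learning the arm minutes earlier cannot change those facts, only the answer.

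It may also be said that switching order partway creates two kinds of baseline, partly aligned with site because Zomba joined only in mid-2015. That is true. However, randomization is 1:1:1 and stratified by site, so the difference in timing should be balanced across arms.

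**Conclusion.** The point holds as a minor weakness of sequence. Three effort-dependent or reported values labelled baseline are taken when the arm can be known, with no earlier value scheduled. The practical consequence is limited to acuity, through the CQ discontinuation endpoint. Performance score and bednet use matter only as baseline descriptors. The primary endpoint and the power are unaffected.

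The document shows that bias is possible, not that it occurred, and its size and direction cannot be derived. The conclusion assumes that the enrollment reading serves as the reference for the two-level change, which Toxicity management does not say, and that the order in the Enrollment section is the one followed.

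A reader might infer that reordering would free the acuity data from open-label influence. It would not: it protects the baseline value only.

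**What to change.** In the Enrollment and Randomization sections, for participants not yet enrolled, have Snellen acuity, performance score and bednet use completed and saved at the enrollment visit before the randomization system releases the arm. In the dataset, flag the values already collected as post-randomization, so that baseline tables and any later use can distinguish the two timings.

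Because assignment is in real time and the measurements already belong to this visit, no procedure, staff or visit is added. The costs are a procedural amendment, a sequence check in the electronic case report form, and two baseline timings across the trial. The benefit reaches at most the 500–600 added participants, and fewer if some were already enrolled. The clinical rule for stopping CQ is not touched.
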